**Methods:**

This multi-centre randomised controlled trial will recruit adults with an acute exacerbation of bronchiectasis requiring hospital admission. Participants will be randomised to receive one of three interventions: ACBT, O-PEP therapy, and walking with huffing. Outcome measures including sputum volume during and 1-h post ACT session, and 24-h sputum, as well as health status, HRQOL and exercise capacity will be completed during inpatient stay on day 2 and day 6 of admission, and within 24 h of hospital discharge. Time to first exacerbation, and time to first hospitalisation will be monitored via monthly phone calls for six months post hospital discharge. Health status and HRQOL will be assessed after discharge at two and six months, and exercise capacity will be assessed at six months post hospital discharge.

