### Participants

Participants will be adults (age 18 years and over) admitted to one of two collaborating private hospitals in Brisbane, Australia, with an acute exacerbation of bronchiectasis, defined by internationally accepted criteria [7]. Exclusion criteria include: primary diagnosis of a respiratory condition other than bronchiectasis, breathing through an artificial airway or requiring non-invasive ventilation within 48 h of hospital admission, or any contraindication to ACBT or O-PEP therapy, including undrained or drained pneumothorax within the last 6 months, post lung lobectomy or lung transplant, haemodynamic instability or severe cardiovascular disease, undrained empyema or lung abscess, active haemoptysis, middle ear infection, previous recruitment and completion/withdrawal from this study, or hyper-reactive airways as diagnosed by a respiratory physician during the hospital admission [41–43]. Potential participants requiring high flow oxygen therapy will still be eligible to participate. A recent hospital admission/exacerbation will not exclude potential participants from being included in the study.

Participants will be assessed for potential inclusion in the first 48 h of hospital admission; if they meet any of the exclusion criteria at this time, they will be deemed ineligible and not reassessed for inclusion later in their hospital admission.

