### Allocation

Participants will be randomly assigned to one of three groups, based on a computer-generated random sequence, with the allocation stratified by participant self-reported usual volume of sputum production (low volume (< 1 teaspoon sputum per day when well) or high volume (> 1 teaspoon sputum per day when well) [44]) to ensure a balance between groups in this characteristic. The computer-generated random allocations will be placed into numbered sequences (one for each strata) of opaque envelopes by the chief investigator, which will only be opened by the treating physiotherapist once baseline measures are completed. Only participants and treating physiotherapists will have knowledge of the group allocation. Blinding of assessors to treatment allocation will be achieved through the assessor not accessing medical documentation for the participant, participants being requested to place any handouts or equipment out of sight (e.g. in a drawer) prior to the assessor entering the room, and the participants being asked not to discuss any intervention with the assessor. The assessors will report any instances of unblinding and these will be recorded. The assessors will be senior cardiorespiratory physiotherapists who are not involved in the patient’s care during the admission.

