#### Statistical methods

Data analysis will be performed using SPSS V.28 (SPSS, Chicago, Illinois, USA). Data will be analysed using intention-to-treat principles, with alpha set at 0.05 for inferential analyses.

Data will be described as mean (standard deviation) or median (interquartile range) for continuous outcomes depending on distribution, and as frequency (percentage) for categorical outcomes. Demographic data, including age, pseudomonas aeruginosa colonisation, bronchiectasis severity scores and QoL-B scores will be compared to findings from the Australian Bronchiectasis Registry to determine external validity of the study findings. Where participants have a comorbid respiratory condition (such as Asthma or COPD), this will be noted and reported in the data analysis, and considered during interpretation of the findings of the study and when discussing the generalisability of findings.

The primary outcome, between-group difference in sputum volume over a 24-h period will be assessed using mixed-effects linear regression models, with treatment group and time included as main effects, and a group-by-time interaction term. Participant will be included as a random effect to account for the repeated measures nature of the data.

Secondary outcome measures with continuous outcomes will be analysed using linear regression, with binary outcomes using logistic regression, and with count outcomes using Poisson regression models. Repeated measures models will be used when appropriate. When data does not fit regression assumptions, non-parametric methods such as the Kruskal–Wallis test will be used to compare differences in scores on each instrument between groups at each of the different time points. Time-to-event outcomes, such as time to first recurrence of an exacerbation following discharge from initial hospital admission, will be visualised using Kaplan Meier survival curves and analysed using Cox proportional hazards regression.

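### The stated primary model adjusts for neither the sputum-volume stratum used in allocation nor the hospital; adding both is a cheap improvement whose benefit is modest and conditional

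*Protocol article*

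**What the plan says.** All references are to the protocol article.

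- **Abstract, Methods, and Participants:** the trial is multi-centre, and participants are "admitted to one of two collaborating private hospitals in Brisbane, Australia".
- **Allocation:** randomisation to three arms is done "with the allocation stratified by participant self-reported usual volume of sputum production", in two categories (low and high). No other stratifier is named. The chief investigator places the allocations in opaque envelopes, in "numbered sequences (one for each strata", and the treating physiotherapist opens them after baseline. The section describes no blocking and does not say where the envelopes are kept.
- **Statistical methods:** the between-group difference in 24-hour sputum is analysed by mixed-effects linear regression "with treatment group and time included as main effects, and a group-by-time interaction term". The only random term is for participant: "Participant will be included as a random effect to account for the repeated measures nature of the data". Neither hospital nor the sputum-volume stratum is listed.
- **Sample size:** 17 per group (51 in all) for a 15 ml difference with SD 15 ml, power 0.80 and alpha 0.05; 90 are sought to allow for 40% attrition.

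**The concern.** Two factors with a plausible bearing on 24-hour sputum are left out of the stated primary model.

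The first is usual sputum volume. The plan thought it important enough to stratify on so that the arms would be balanced, but does not analyse by it. Where stratification does balance a prognostic factor, a linear model without that factor leaves its variation in the error term, so standard errors tend to be too large and the comparison less sensitive than the design allows.

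The second is hospital. The supervised sessions are given by physiotherapists at each site. The background treatment described under Usual care is set by the treating physician and ward physiotherapist, so mean sputum could differ between sites. Hospital is neither a stratifier nor a model term, so the arms can differ in hospital mix by chance and nothing in the stated analysis takes that out.

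Precision is at stake in a small three-arm trial. The Sample size section itself concedes that the recruitment target may not be met.

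**Working it through.** **Inputs from the protocol article:** 3 arms; 17 evaluable per arm; 90 sought (30 per arm); difference 15 ml; SD 15 ml; power 0.80; alpha 0.05 (Sample size); 2 hospitals (Participants).

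**Assumed, because the article gives no figure:** the recruitment split between hospitals (50:50, with 70:30 as a check) and the between-hospital difference D in mean 24-hour sputum (5 and 10 ml, with 0 as the no-effect case).

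**1. The plan's own figure.** A two-sided two-sample t-test with standardised difference 15/15 = 1 has power 0.807 at 17 per group and 0.781 at 16. So 17 per group reproduces. For attrition, 51/(1 − 0.40) = 85, or 29 per arm = 87 with whole numbers per arm. The stated 90 is slightly generous: 90 × 0.60 = 54, which exceeds 51.

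**2. Imbalance by hospital.** If allocation is independent of hospital and a share p of patients comes from one hospital, the between-arm difference in that share has SD = √(2p(1 − p)/n).

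- p = 0.5, n = 17: √(0.5/17) = 0.171
- p = 0.5, n = 30: √(0.5/30) = 0.129
- p = 0.7, n = 17 and 30: 0.157 and 0.118

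In simulation, two given arms differ by at least 20 percentage points with probability 0.19 to 0.23 at 17 per arm and 0.12 to 0.16 at 30. The largest gap among the three arms reaches 20 points with probability 0.38 to 0.45 at 17 per arm and 0.27 to 0.33 at 30. Each range covers the two splits.

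**3. Shift in an unadjusted arm contrast from a 1-SD imbalance.** This is D × SD. With p = 0.5:

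- D = 5 ml: 5 × 0.171 = 0.86 ml (n = 17); 5 × 0.129 = 0.65 ml (n = 30)
- D = 10 ml: 1.71 ml (n = 17); 1.29 ml (n = 30)

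The shift is as likely to favour one arm as the other.

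**4. Effect of a hospital term on power at 17 per arm.** Take 15 ml as the total SD, including any hospital variation. The residual variance after adjustment is then 225 − p(1 − p)D².

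| p | D (ml) | Hospital share of variance | Residual SD (ml) | Power without term | Power with term (approx.) |
|---|---|---|---|---|---|
| 0.5 | 5 | 6.25/225 = 2.8% | √218.75 = 14.79 | 0.807 | 0.818 |
| 0.5 | 10 | 25/225 = 11.1% | √200 = 14.14 | 0.807 | 0.850 |
| 0.7 | 5 | 5.25/225 = 2.3% | √219.75 = 14.82 | 0.807 | 0.816 |
| 0.7 | 10 | 21/225 = 9.3% | √204 = 14.28 | 0.807 | 0.843 |
| any | 0 | 0 | 15 | 0.807 | no gain |

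These powers ignore the degree of freedom spent on the term.

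If 15 ml were instead the within-hospital SD, the unadjusted SD at p = 0.5 would be √231.25 = 15.21 ml (D = 5) or √250 = 15.81 ml (D = 10). Power without the term would then be 0.796 or 0.765. In either case the difference the term makes is about 1 to 4 power points.

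**5. Sputum-volume stratum.** The variance-share formula p(1 − p)D²/225 serves equally here, but the article gives neither the split between low and high producers nor the difference between them. No figure is therefore put on this part.

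**The case against.** **An analysis plan may exist and may add covariates.** That is true, and the article does not say hospital will be excluded. But the article does list the terms of the primary model, and as listed the model leaves out the factor the trial stratifies on. Improving a stated model is a fair comment; this is not a complaint about missing detail.

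**No hospital effect is documented.** This stands. Both sites are private hospitals in one city, usual care is described once for everyone, and technique instructions and session end points are common to both. The 5 and 10 ml gaps are assumptions. If the true gap is nil, nothing is lost.

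**A constant hospital shift is absorbed by the participant effect and cancels from the group-by-time contrasts.** With complete data this is right for changes over time. It does not cover the between-group difference at a given time point, where a difference in hospital mix remains.

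**Stronger readings a reader might take from the text.** None is supported.

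- *Both hospitals draw from one shared sequence.* One sequence per stratum makes this a natural reading, but the Allocation section does not say so, nor where envelopes are held. A condensed article may leave that to the full protocol.
- *Splitting the sequence between sites breaks the blocking.* No blocks are described. If randomisation within stratum is simple, splitting does no harm.
- *Precision is certainly lost, or the result is biased.* Any loss depends on an undocumented hospital difference, and the planning SD may already contain it. Chance imbalance under valid randomisation widens uncertainty but does not bias the comparison.

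**Conclusion.** The point holds in a limited form. As stated, the primary model adjusts for neither the allocation stratum nor hospital in a two-hospital trial. Imbalance by hospital is not rare at 17 to 30 per arm, but its consequence is small: about 0.6 to 1.7 ml for a 1-SD imbalance, against the 15 ml target, and roughly 1 to 4 power points at 17 per arm. Both figures rest on an assumed 5 to 10 ml hospital difference. The imbalance figures also assume a 50:50 recruitment split; a 70:30 split gives slightly smaller values. With no hospital difference there is no effect. The gain from the sputum-volume term cannot be sized from the article; the case for it is that the analysis should follow the factor used in the randomisation. This is a worthwhile, inexpensive refinement. It is not a threat to the trial's validity, and the stated sample size does not need to change because of it.

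**What to change.** Add sputum-volume stratum (low or high) and hospital as fixed effects in the primary mixed model, and state this before the analysis. Both variables are already held by the trial. The cost is about two degrees of freedom: with 51 evaluable participants in three arms, the between-participant residual goes from 51 − 3 = 48 to 46. This can be done even if envelopes are already in use.

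State whether envelope sequences are held separately at each hospital. If they are not yet in use, a separate sequence per stratum at each hospital (2 × 2 = 4 in all) is optional. It needs two more envelope sets if only two sequences are now planned. The downside is smaller cells: on average about 13 evaluable (51/4) or 22 to 23 recruited (90/4 = 22.5) participants per sequence, spread over three arms. If blocking is used, cells of this size may end with incomplete blocks, and small blocks would make allocations easier to predict for the treating physiotherapists, who know the assignments.

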### Outcomes

All participants will be assessed at three time points during their hospital admission, and then once per month for six months post hospital discharge, by an assessor blinded to group allocation. The assessments to be conducted are described below. If participants withdraw from the study prior to completing the six months follow-up, their data will be included in data analysis up until the point of withdrawal unless specially requested otherwise by the participant.

The primary outcome of sputum volume, measured by the wet weight of sputum (grams), will be assessed three times during hospital admission on day 2, day 6, and within 24 h of hospital discharge. On each occasion, sputum will be collected during a physiotherapist-supervised ACT session, in the hour following the ACT treatment session, and over a 24-h period following the session. Twenty-four-hour sputum volume has been shown to be a responsive outcome measure during acute exacerbations of bronchiectasis [29, 43, 45]. Either an increase in sputum volume during the session, or one-hour post-session, or a decrease in sputum volume in the following 24-h period will be interpreted as an improvement in sputum clearance [29, 30, 43].

Secondary outcomes to be assessed include health status (Bronchiectasis Health Questionnaire) [46], disease-specific HRQOL (Quality of Life-Bronchiectasis questionnaire (QoL-B) and Leicester Cough Questionnaire) [47, 48] and exercise capacity (6 min walk test [49]). Each of these measures will be completed three times during hospital admission (on day 2, day 6, and within 24 h of hospital discharge). Additionally, health status and HRQOL will be assessed at two- and six-months post hospital discharge. Exercise capacity will be completed at six months post hospital discharge. The questionnaires will be completed via pen and paper during hospital admission, then via phone at two months post hospital discharge. At six months the questionnaires will be completed via paper and pen in the clinic or via phone if participants are unable to attend in person. The questionnaires for health status and HRQOL have been shown to be valid and reliable measures in individuals with bronchiectasis [46–48, 50].

Number of exacerbations, number of hospital admissions and time to first exacerbation and hospital admission will be collected for six months post hospital discharge from the date of discharge. A blinded assessor will complete monthly phone calls using questions investigating clinical status in the last month including symptoms, hospital admissions and use of antibiotic therapy (and comparing participant responses to these questions to the international definition of an exacerbation for bronchiectasis [7]. Participants will also complete the Bronchiectasis Exacerbations and Symptoms Tool (BEST) daily from time of discharge from hospital to six month follow-up [51]. The BEST tool is a symptom diary, designed to detect bronchiectasis exacerbations, which involves six questions regarding breathlessness, sputum volume, cough, fatigue, sputum colour and cold and flu symptoms. It has been shown to be responsive to identifying exacerbations at onset and recovery for individuals with bronchiectasis [51].

### Interventions

Participants will be randomly allocated to one of three groups, which are based on the intervention to be received:The ACBTO-PEP therapyWalking and FET (control)

The instructions for use of each ACT will be informed by practice guidelines [52] and previous studies [15, 23]. Whilst inpatients, participants will be instructed to complete their allocated ACT three times daily, once supervised by a physiotherapist, and twice independently. On discharge, participants will be instructed to continue their allocated technique twice daily. Participants will be instructed to cease their usual airway clearance therapy (if any) and exclusively complete the allocated technique for the duration of the study period. Compliance will be encouraged and monitored through daily interviews (inpatient stay), provision of written instructions, and monthly phone calls (upon discharge). The phone calls will collect information regarding adherence to ACT and clinical status in the previous month, including changes in respiratory symptoms, any hospital admissions or use of antibiotics.

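### The monthly calls assigned to a blinded assessor appear also to collect and encourage adherence to the allocated technique, which is likely to unblind the exacerbation outcomes

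*Protocol article*

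**What the plan says.** Three sections of the protocol article bear on the monthly calls.

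- **Outcomes.** Follow-up assessments take place "once per month for six months post hospital discharge, by an assessor blinded to group allocation". For exacerbations and admissions the section adds: "A blinded assessor will complete monthly phone calls using questions investigating clinical status in the last month including symptoms, hospital admissions", together with antibiotic use. The exacerbation decision is reached by "comparing participant responses to these questions to the international definition of an exacerbation for bronchiectasis".
- **Interventions.** On adherence: "Compliance will be encouraged and monitored through daily interviews (inpatient stay), provision of written instructions, and monthly phone calls (upon discharge". On the content of those calls: "The phone calls will collect information regarding adherence to ACT and clinical status in the previous month". The clinical items then listed are respiratory symptoms, admissions and antibiotics.
- **Allocation.** "Only participants and treating physiotherapists will have knowledge of the group allocation". Assessor blinding rests on the assessor not opening the medical record, on handouts and equipment being hidden, and on "the participants being asked not to discuss any intervention with the assessor". Unblinding is to be reported by the assessor and recorded.

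**The concern.** An outcome assessor who also asks how a participant is getting on with the allocated technique, and encourages its use, is likely to learn which technique it is. The same person then decides whether the reported symptoms meet the exacerbation definition. Exacerbation rates over six months are among the stated secondary aims, and the Abstract presents the long-term outcomes as part of the trial's contribution. If the caller knows the arm, the trial would report as blinded a judgement that its own procedure had opened to detection bias. The questionnaires at two months are also completed by phone and are exposed in the same way if this assessor administers them.

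**Working it through.** No figure in the plan bears on this point, so the check is a comparison of passages.

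**1. Is it the same call?**

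| Feature | Outcomes | Interventions |
|---|---|---|
| Frequency | monthly | monthly |
| Period | six months after discharge | after discharge |
| Clinical items | symptoms, admissions, antibiotics | symptoms, admissions, antibiotics |
| Adherence | not listed | listed |
| Encouraging compliance | not mentioned | yes |
| Caller | blinded assessor | not named |

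Timing and clinical items coincide, and no second series of calls or second caller is described. One call is the natural reading, but it is an inference.

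**2. Would talk about adherence disclose the arm?** The three intervention sections give these home regimens:

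- ACBT: breathing cycles, twice daily.
- O-PEP: an Aerobika device, twice daily.
- Control: walking towards 30 min/day, with FET.

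Any mention of a device, a breathing cycle or minutes walked identifies the arm. Encouraging someone to keep to a regimen is hard to do without naming it.

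**3. Do the safeguards work by telephone?** Staying out of the medical record and hiding equipment do not stop a participant from naming the technique on the phone. The one safeguard that can work in a call is the request not to discuss the intervention. An adherence enquiry by the assessor works against it.

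**4. Does the order of questions settle it?** The order is not given. Suppose the same assessor makes all six calls (an assumption). Then 6 − 1 = 5 of the 6 monthly judgements come after at least one earlier adherence enquiry, whatever the order within each call. Asking about adherence last protects that month's judgement, but later ones only if the item does not reveal the technique.

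**5. Which outcomes are exposed?**

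- Exacerbation counts and time to first exacerbation: exposed. The Introduction defines an exacerbation as worsening of at least three listed symptoms for at least 48 hours, and the caller applies this to self-reported answers.
- Two-month phone questionnaires: exposed if the same assessor administers them, which is not stated.
- Hospital admissions: asked about in the same call, but largely factual.
- Primary outcome: not exposed. Sputum is weighed during the admission, before the monthly calls.

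**The case against.** The other side has several good arguments.

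- **The caller is inferred.** The Outcomes list of what the blinded assessor asks omits adherence, and the Interventions section does not say who calls. This stands, and the point must be stated as an inference.
- **The passages can coexist.** A reader might infer that the three sections cannot all be followed, or that the arm is always revealed before an exacerbation is judged. The document supports neither. Question order and wording are not given, and the Interventions section sets a twice-daily frequency after discharge for every arm, so adherence could be asked as sessions completed without naming a technique. What remains is that no such wording is specified and that the calls are also meant to encourage compliance, which is harder to keep neutral.
- **The safeguards describe the ward.** Drawers and entering the room are inpatient details. Extending the no-discussion request to phone calls is reasonable but not stated. However, the Outcomes section claims blinding for the monthly follow-up as well.
- **Participants know their arm.** They supply all the symptom data, so these outcomes are partly open-label even with a perfectly blinded caller. The daily BEST diary is a second source, but participants complete that too. This limits what caller blinding can achieve. It does not remove the added risk from an unblinded judgement.
- **Unblinding is recorded.** Recording detects the problem but does not prevent it.

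**Conclusion.** The conflict is real, but it is a risk to blinding and not a proven failure. On the likeliest reading, following the plan as written has the blinded assessor collect and encourage adherence in the call used to judge exacerbations. That is likely to unblind the assessor for exacerbation counts and time to first exacerbation. It extends to the two-month phone questionnaires only if the same assessor administers them.

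The conclusion rests on one assumption: that the calls in Outcomes and Interventions are the same call with the same caller.

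A reader might want to express the problem as the share of participants unblinded by the sixth call. The document gives no disclosure rate per call and nothing on whether disclosures are independent, so any such figure would be invented. Nor can a bias in any outcome be calculated. The point concerns secondary outcomes only, and merits correction mainly because correction is cheap.

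**What to change.** Reconcile the Allocation, Outcomes and Interventions sections.

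- **Preferred:** take adherence collection and encouragement out of the blinded assessor's call. Give them to the treating physiotherapist, who already knows the allocation, in a short separate contact. Giving this task to the research assistant would conflict with Allocation, which restricts knowledge of the arm to participants and treating physiotherapists.
- **If one call is kept:** lock the exacerbation form first. Then ask a single technique-neutral item, the proportion of prescribed sessions completed, with no coaching by the assessor. Minutes walked or use of a device should not be asked.
- **In either case:** enter any disclosure during a call in the unblinding record that Allocation already provides for.

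The cost is a short extra contact by existing staff under the first option, or less detailed adherence data under the second. Neither changes treatment or sample size.
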